### fMRI assessment

Each multiparametric fMRI scan will consist of sequences: DCE-MRI, DWI-MRI, BOLD-MRI, quantitative T1-weighted and T2-weighted MRI and will be carried out at three time points- prior to CRT (RT planning), week 2 of CRT (fraction 10) and week 5 of CRT prior to brachytherapy (fraction 25). Delineations of the gross tumour volume (GTV) using T2-weighted MR sequences for each case will be performed by a clinical oncologist and verified by a consultant radiologist. The GTV tumour volume reduction rate (TVRR) will be determined between these three time points as defined on anatomic sequences. Kinetic modelling will be applied in DCE-MRI images to assess quantitative kinetic parameters in the GTV related to blood volume, blood flow, interstitial volume and tissue permeability. DWI-MRI sequences will be used to calculate ADC maps to provide information related to tumour cellularity and necrosis. Signal changes on BOLD-MRI sequences will be used to calculate the T2 relaxation rate reflecting intravascular deoxyhaemoglobin concentration, and therefore, providing information related to tumour oxygenation. Anatomic T1 and T2 imaging will be used for radiomic feature extraction and textural analysis through quantitative mapping.

The details of each MRI and radiomic parameter are summarised in table 1.

**Table 1 T1:** fMRI sequences with corresponding parameters used to assess cervical tumour response during radical chemoradiotherapy

Imaging	Parameters	Biological correlates
DCE-MRI	Extravascular extracellular space volume fraction V_e_ (%)	Blood volume, blood flow, interstitial volume and tissue permeability
	Transfer constant K^trans^ (/min)	
	Rate Constant k_ep_ (/min)	
	Blood volume fraction v_p_ (%)	
DWI-MRI	Apparent diffusion coefficient ADC (um^2^/s)	Tumour cellularity, architectural complexity and necrosis
BOLD-MRI	BOLD-based reversible transverse relaxation rate R2^*^ (/s)	Intravascular deoxyhaemoglobin concentration
T1 and T2 weighted MRI	Relaxation times (/s)	Tissue physical characters affecting water relaxation and anatomical information
T2-weighted±DWI MRI (Grey level co-occurrence matrix)	Second-order Haralick textural radiomic features	Intratumoural heterogeneity

BOLD, blood oxygen-level dependent; DWI, diffusion-weighed imaging; fMRI, functional MRI.

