#### Secondary outcomes

To evaluate sensitivity and specificity quantitative parameters derived from DCE-MRI, DWI-MRI and BOLD-MRI as predictors of overall survival at 2 years in patients with locally advanced cervical cancer after CRT.To evaluate sensitivity and specificity quantitative parameters derived from DCE-MRI, DWI-MRI and BOLD-MRI as predictors of the TVRR in response to CRT of patients with locally advanced cervical cancer.To apply radiomics for derivation of textural imaging features as predictors of progression-free (local, nodal, systemic), overall survival and TVRR after CRT for cervix cancer.To correlate temporal changes in quantitative MRI parameters during CRT with molecular markers from tissue biopsies and CTCs isolated from peripheral blood samples.To explore the feasibility of using quantitative MRI parameters to provide a roadmap in identifying high-risk regions for potential dose escalation with radiotherapy.

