### Statistical analysis

Using logistic and Cox regression models the study will evaluate:

Different thresholds and temporal changes of fMRI parameters (DCE-MRI, DWI-MRI and BOLD-MRI) at various time points during cervical CRT can predict progression-free (local, nodal, distant) survival.Different thresholds and temporal changes of fMRI parameters (DCE-MRI, DWI-MRI and BOLD-MRI) at various time points during cervical CRT can predict response to treatment as defined by TVRR.Different thresholds and temporal changes of fMRI parameters (DCE-MRI, DWI-MRI and BOLD-MRI) at various time points during cervical CRT can predict overall survival.Different radiomics features can predict response to cervical CRT in terms of TVRR, progression-free (local, nodal, distant) survival and overall survival.Different thresholds and temporal changes of fMRI parameters (DCE-MRI, DWI-MRI and BOLD-MRI) at various time points during cervical CRT can predict changes in immunohistochemical markers of hypoxia and epithelial mesenchymal transition.

For each of the above regression analyses, a univariate logistic regression reporting the OR with 95% CI and p value from the likelihood ratio test will be performed. All covariates (fMRI parameters and radiomic features in table 1) and demographics) with a p<0.1 will be entered into a multivariate, forward conditional logistic regression and subsequently a p<0.05 will be considered statistically significant. The utility of the final prognostic model will be evaluated using sensitivity, specificity and area under the receiver operating characteristic curve.

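### Tumour volume reduction rate is continuous, but the plan fixes a binary-outcome analysis for it and sets no time order between its predictors and the reduction they are meant to predict

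*Protocol article*

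**What the plan says.** All places are in the Method section of the protocol article.

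- **fMRI assessment, outcome.** There are three fMRI scans: before CRT, at fraction 10 and at fraction 25. "Delineations of the gross tumour volume (GTV) using T2-weighted MR sequences for each case" are made by an oncologist and checked by a radiologist. "The GTV tumour volume reduction rate (TVRR) will be determined between these three time points as defined on anatomic sequences". No responder threshold is given.
- **fMRI assessment, predictors.** "Kinetic modelling will be applied in DCE-MRI images to assess quantitative kinetic parameters in the GTV". "Anatomic T1 and T2 imaging will be used for radiomic feature extraction and textural analysis through quantitative mapping". No region of interest is named for ADC or R2*.
- **Secondary outcomes.** Sensitivity and specificity of the DCE, DWI and BOLD parameters are to be evaluated "as predictors of the TVRR in response to CRT of patients with locally advanced cervical cancer".
- **Statistical analysis.** Only logistic and Cox models are named. One listed question is whether thresholds and temporal changes of the parameters, at various time points during CRT, "can predict response to treatment as defined by TVRR". A second asks the same of radiomic features. A third asks whether the parameters "can predict changes in immunohistochemical markers of hypoxia and epithelial mesenchymal transition". A univariate logistic regression with an odds ratio is then prescribed for each listed analysis, followed by a p<0.1 screen and forward selection.

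**The concern.** There are two separate issues.

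**Scale.** A percentage or rate of volume change takes a value for every patient with the scans. An odds ratio, a sensitivity and a specificity exist only once that value has been cut into two groups. Cutting treats patients just either side of the threshold as opposites and all patients on one side as alike. With 40 patients, the information lost is worth having. The recurrence analysis rests on an expected 14 events, whereas volume reduction is measured on every scanned patient.

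**Time order.** The scans that supply the predictors are the same three that define the outcome. Nothing in the text confines predictors to scans made before the reduction being predicted. A parameter read from the closing scan cannot be known before the response is known. For DCE parameters, and for features from the T2 images on which the GTV is drawn, contouring error could also enter both sides. The Future work section intends the identified parameters to feed a risk-stratification model, a validation study and then a randomised trial. A marker that only accompanies response should not go forward as a predictor of it.

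**Working it through.** **1. The plan's own figures.** 30 patients per year × (1 − 0.30) = 21 per year; 2 × 21 = 42 over 24 months, against a target of 40. Events: 40 × 0.35 = 14. Both reproduce. The 14 are recurrences and do not concern TVRR; the article gives no figure for the TVRR analysis.

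**2. Does the text force a binary TVRR?** The outcome definition is a change in volume. The metric in the Secondary outcomes is sensitivity and specificity. The models named are logistic and Cox, and the odds-ratio instruction covers every listed analysis, TVRR included. Cox regression does not suit a volume change between fixed scans. The only prescribed route is therefore logistic, on a dichotomised TVRR.

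**3. Information lost by cutting.** Assume a normally distributed outcome with a proportion p on one side of cut c. The asymptotic efficiency relative to the continuous analysis is φ(c)²/[p(1−p)].

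- Median split: 0.3989²/0.25 = 0.637, so 40 patients are worth about 40 × 0.637 = 25.5.
- 30/70 split: 0.3477²/0.21 = 0.576, or about 23.0.
- 25/75 split: 0.539, or about 21.5.

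**4. Power at n = 40.** Simulation with 3,000 runs per setting, one normal predictor, all 40 patients evaluable, two-sided 0.05. The correlations are assumptions; the article gives none.

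| Assumed correlation | Linear | Logistic, median split | Logistic, 30/70 split |
|---|---|---|---|
| 0.3 | 49% | 35% | 30% |
| 0.4 | 75% | 56% | 51% |
| 0.5 | 92% | 77% | 72% |

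A second simulation, with a 25/75 split in place of 30/70, gives 48/33/30%, 74/56/49% and 93/78/70% in the same order. With no true association, its error rates are 5.1%, 5.9% and 6.1%, so the linear model's advantage does not come from a looser test.

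**5. If the cut were chosen from the data.** Taking the best of three TVRR cuts (quartiles and median) for one null predictor gives p<0.05 in 13.9% of runs, against 5.9% with the median cut alone. This applies only if no cut is fixed in advance.

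**6. Time order.** The article does not enumerate predictor forms. Assume three levels and three pairwise changes per parameter. Their timing against each possible TVRR interval is then:

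| TVRR interval | Known at or before the start | Measured inside the interval | Uses the closing scan | Uses a later scan |
|---|---|---|---|---|
| Pre-CRT to fraction 10 | 1 | 0 | 2 | 3 |
| Pre-CRT to fraction 25 | 1 | 2 | 3 | 0 |
| Fraction 10 to 25 | 3 | 0 | 3 | 0 |

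The wording admits every cell.

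**7. What a same-scan relation can look like.** Suppose a fraction-25 parameter merely tracks residual log volume at fraction 25 and carries nothing else (assumed SDs: 0.8 for log baseline volume, 0.6 for log reduction). Against median-split TVRR, for a correlation with residual volume of 0.2 / 0.4 / 0.6, it passes the p<0.1 screen in 17% / 34% / 61% of runs and reaches p<0.05 in 9% / 24% / 48%. With zero correlation the rates are 11% and 6%.

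**The case against.** The study is exploratory, disclaims formal power, and plans later validation. A full protocol or SAP may fix a responder cut-off and pair predictor times with outcome intervals. Logistic regression on a prespecified clinical cut-off is valid, only less efficient. All of that stands, and it limits severity. It does not remove the point, because the article commits to the model family and the metric. A SAP that supplied a cut-off would still carry the loss, and one that used only linear regression would depart from the stated secondary outcome.

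A reader might infer more than the article supports:

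- **That fraction-25 parameters will be used to predict TVRR to fraction 25.** No sentence pairs them. The wording permits the pairing and nothing excludes it. Pre-CRT predictors, and fraction-10 predictors of later shrinkage, are properly prospective.
- **That all parameters share the GTV contour with the outcome.** The region is stated only for DCE. For radiomics, the overlap is that T2 imaging supplies both features and contour.
- **That concurrent predictors will win the selection.** Competition between early and late predictors was not computed. The screening rates above depend on an assumed correlation.
- **That immunohistochemical change is also wrongly dichotomised.** Its scale is not given. If staining is scored positive or negative, logistic regression may be appropriate.
- **That TVRR is the only endpoint free of the 14 events.** The immunohistochemical and CTC correlations do not depend on them either.

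**Conclusion.** The point holds, at moderate severity. On the text alone, TVRR is continuous, its prescribed model and metric are binary, and no continuous alternative is offered. The cost is lost efficiency rather than an invalid test: about 36% of the information at a median split (1 − 0.637) and about 42% at a 30/70 split (1 − 0.576). At an assumed correlation of 0.4, that is 19 to 24 percentage points of power (75 − 56 and 75 − 51). These sizes assume normality, a single predictor tested at 0.05 and 40 evaluable patients; the plan's screening and forward selection were not modelled in the power comparison. The time-order part is an ambiguity to close, not a demonstrated error: as worded, the plan lets a concurrent association be reported as prediction. Only secondary outcomes are touched; the primary progression-free survival analysis is unaffected.

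**What to change.** - **Model.** Make the main TVRR analysis a linear regression of log (or cube-root) residual GTV on the parameter, adjusted for GTV at the start of the interval on the same scale. Report slope, confidence interval and R-squared.
- **Metric.** Keep sensitivity and specificity for TVRR at most as a supplementary analysis, at one cut-off fixed in advance.
- **Time order.** Use only parameters measured at or before the start of the interval. Pre-CRT values may predict reduction to fractions 10 and 25. Fraction-10 values and the pre-CRT-to-fraction-10 change may predict the fraction-10-to-25 reduction. Label same-scan relations as concurrent correlation.
- **Immunohistochemistry.** If change is scored on a continuous or ordinal scale, analyse it on that scale.

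The cost is a reworded secondary outcome as well as reworded analysis text, and fraction-25 values are lost as TVRR predictors. No new patients, scans or data are needed.

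### Texture features are tested without tumour volume among the candidate covariates, so a size surrogate cannot be told apart from a marker of heterogeneity

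*Protocol article*

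**What the plan says.** The Statistical analysis section of the protocol article lists the radiomics question as "Different radiomics features can predict response to cervical CRT in terms of TVRR, progression-free (local, nodal, distant) survival and overall survival". For each regression question, the first step is "a univariate logistic regression reporting the OR with 95% CI and p value from the likelihood ratio test will be performed". The second step is a forward conditional logistic model, and its candidates are written out: "All covariates (fMRI parameters and radiomic features in table 1) and demographics) with a p<0.1 will be entered". After that, "subsequently a p<0.05 will be considered statistically significant".

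Table 1 (fMRI assessment section) names the texture variables as "Second-order Haralick textural radiomic features" from the grey-level co-occurrence matrix, and gives their biological correlate as "Intratumoural heterogeneity". Tumour volume is not a row of that table, and neither volume nor stage is named as a covariate elsewhere.

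The volume data exist. The fMRI assessment section states: "Delineations of the gross tumour volume (GTV) using T2-weighted MR sequences for each case will be performed by a clinical oncologist". It continues: "The GTV tumour volume reduction rate (TVRR) will be determined between these three time points as defined on anatomic sequences". The article therefore uses GTV volume to build an outcome, but does not list it as a predictor.

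**The concern.** A univariate likelihood ratio test has a null of no marginal association of any kind between the feature and the outcome. Co-occurrence features are computed inside the GTV. Many of them depend on how many voxels the region holds and, under some binning rules, on the grey-level range, which tends to widen as the region grows. If larger tumours also progress more often, such a feature can be associated with outcome because it carries tumour size.

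Eligibility runs from FIGO Ib2 to IVa, so a wide spread of sizes is to be expected. The forward selection step does not help, because it cannot pick a variable that is not a candidate.

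What is at stake is interpretation and added value. A feature selected in this way could be described by its Table 1 label, or taken into the model that the Future work section plans to validate, while adding little to a volume that the team already measures.

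**Working it through.** **The plan's own figures (Sample size and power).** Events: 40 × 0.35 = 14, as stated. Accrual: 30 × (1 − 0.30) = 21 per year, as stated. The checks below use N = 40 and 35% events.

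**Step 1: do texture features vary with region size?** The article does not say, so this was simulated. The same stationary random texture was placed in spherical regions of about 550 to 17,000 voxels (32 grey levels, 400 draws). Spearman correlation of each feature with region volume:

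| Feature | Fixed-width bins | Bins over the region's own range |
|---|---|---|
| Entropy | 0.45 | −0.72 |
| Energy | −0.38 | 0.68 |
| Contrast | 0.14 | −0.81 |
| Homogeneity | −0.05 | 0.79 |
| Correlation | 0.41 | 0.30 |

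A second set of simulated tumours assumed a median GTV of 40 cm³, a log-SD of 0.7, and 32 or 64 grey levels over the GTV range. With identical texture, absolute correlations with log volume were about 0.5–0.7 for contrast and homogeneity, 0.2–0.6 for entropy and energy, and at most 0.28 for the correlation feature. When patients were also allowed to differ in true texture, the range was about 0.0–0.6. Size dependence is therefore real for many features, but its strength and even its sign depend on the feature and the binning.

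**Step 2: how often would a pure size surrogate reach p<0.05?** Let V be standardised log volume and T the texture feature.

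- Outcome: logit P(event) = a + log(OR) × V, with a set so that 35% have events. T has no effect given V.
- Texture: T = rV + √(1 − r²) × e, with e standard normal.
- Planned test: 2[ℓ(T) − ℓ(intercept)] against chi-square on 1 df.
- Volume-adjusted test: 2[ℓ(V, T) − ℓ(V)] against chi-square on 1 df.

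Both r and the OR per SD of log volume are assumptions, because the article gives neither. Share of simulated studies (3,000 or 4,000 per cell) with p<0.05 for T in the planned test:

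| Volume OR per SD | r=0.3 | r=0.4 | r=0.5 | r=0.6 | r=0.7 | r=0.8 |
|---|---|---|---|---|---|---|
| 1.5 | 7% | 8% | 10% | 12% | 14% | 16% |
| 2 | 10% | 12% | 17% | 22% | 29% | 34% |
| 3 | 14% | 21% | 27% | 38% | 50% | 63% |

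A further run at OR 2 gave 13%, 21% and 35% for r = 0.4, 0.6 and 0.8. At the p<0.1 screen, the OR 2 figures for those r were 20%, 33% and 46%. With volume in the model, the rate at p<0.05 was 5–7% throughout. If volume has no effect (OR 1), the planned test rejects in 5–6% and there is no inflation. Monte Carlo standard error is about √(0.38 × 0.62 / 3,000) = 0.9 percentage points at the 38% cell.

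**Step 3: what does adjustment cost?** Here texture truly matters (OR 2 per SD) and volume does not. Power at p<0.05 without and then with volume was 0.52 and 0.46 at r = 0.4, 0.51 and 0.36 at r = 0.6, and 0.50 and 0.22 at r = 0.8. A repeat at r = 0.6 gave 0.49 and 0.36.

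**Not covered.** Every simulation used a binary event outcome. None addresses TVRR.

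**The case against.** The strongest reply is that the plan's aim is prediction. For that aim a test of marginal association is a valid screen, since a size-correlated feature that predicts progression does predict it. That stands. A reader might infer that the test is invalid, or that the plan will declare heterogeneity prognostic. The article contains no such decision rule; the only link is the biological-correlate label in Table 1.

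A reader might also infer that all Haralick features follow volume mechanically. The simulations do not support this: under fixed-width bins, contrast and homogeneity are almost unaffected. The article does not state its binning, a detail that an article may fairly leave to the full protocol.

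The size of the effect rests on two assumed quantities. At r = 0.4 and OR 1.5 the planned test rejects in 8–9%, hardly above the adjusted level. The figures at r = 0.8 need a correlation above the 0.0–0.6 seen once patients differ in texture.

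Nor do the documents justify forcing baseline volume into every model. Features from the fraction 10 and fraction 25 scans would follow the GTV at those scans, and Step 3 shows that the power loss is real. The dose-escalation map in the Radiotherapy-related assessment section is built from BOLD, DCE and DWI parameters, so this point does not reach it.

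What the reply leaves unanswered is that the written covariate set gives no means of telling a size surrogate from a feature that adds to size. The study's exploratory status softens the consequence but does not supply that means.

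**Conclusion.** The point holds in a limited form. As written, the radiomics analysis cannot separate texture from tumour size, because GTV volume is not among the named candidates at either step. If volume is prognostic, with an OR of 1.5–3 per SD, and a feature correlates with it at 0.4–0.6, the feature reaches p<0.05 purely as a surrogate in about 8–9% to 38% of studies, against 5–7% with volume in the model. Features weakly tied to size, or a volume with no prognostic effect, give little or no inflation.

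This does not make the planned screen wrong as a test of prediction. It limits what a significant result can be called: neither the Table 1 heterogeneity reading nor a claim of value beyond size follows from it. For TVRR the direction of concern is the same, because outcome and texture region come from the same GTV, but its size has not been quantified. The remedy is an inexpensive improvement, not a repair of an invalid analysis.

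**What to change.** - Keep the planned univariate screen. Add log GTV volume, measured at the same scan as the feature, to the candidate covariates. The contours needed for TVRR already supply it.
- For each radiomic feature that passes the screen for PFS or OS, also report its correlation with that volume and the likelihood ratio test for the feature added to volume.
- Describe a feature as a heterogeneity marker, or as adding to tumour size, only if the volume-adjusted test supports it.
- For TVRR, report the volume-adjusted result as a sensitivity analysis, because TVRR is derived from the same GTV volumes.

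No new data are needed. The cost is one degree of freedom against about 14 events, and lower power in the adjusted test when texture and volume are strongly correlated. A feature that loses significance after adjustment should therefore be reported as not separable from size, rather than as shown to have no effect.

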### Translational biological assessment

Tumour tissues from the diagnostic biopsy and a second biopsy taken at the time of brachytherapy will be collected. The unstained biopsy slides will be stained for immunohistochemical markers of hypoxia (CA IX, GLUT-1), vascularity (VEGF) and epithelial mesenchymal transition (CD44, SOX-2). These molecular markers at various time points will be correlated with imaging parameters and evaluated independently and in combination with respect to prognostic impact. Peripheral blood samples will be taken at the three imaging time points (pre-CRT, fraction 10 and fraction 25 of CRT) for analysis of CTCs. CTCs will be isolated from peripheral blood samples via an optimised enrichment technique using CD45 antibody. Based on branched DNA signal amplification technology, CTCs will be classified into three subpopulations with respect to metastatic potential using epithelial mesenchymal transition markers: epithelial CTCs (EpCAM or CK8), mesenchymal CTCs (vimentin or TWIST) and mixed phenotype CTCs (both markers). The CTC phenotype ratio at various time points will be correlated with imaging parameters and evaluated independently and in combination with respect to prognostic impact (progression-free survival and overall survival).

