### Sample size and power

In the absence of evidence in published literature on which to derive sample size calculations in the context of an exploratory feasibility study, formal statistical power calculations have not been performed. An aim of exploratory studies is to determine feasibility of specific study aspects, subsequently allowing for estimation of sample sizes in the future studies.

The proposed sample size of 40 patients is a convenience-based sampling reflecting the annual estimate of patients with locally advanced cervical cancer likely to be eligible for this study at Mount Vernon Cancer Centre. From January 2019 to December 2019, there were a total of 30 patients with locally advanced cervical cancer treated with radical CRT. Assuming a conservative patient decline/withdrawal rate of 30%, the estimated annual number of complete study accruals is 21. This should enable a total number of 40 patients to be recruited over a period of 24 months. In a mixed population of cervix patients, a 2-year recurrence rate (local, nodal and distant) of 35% is assumed resulting in an estimated number of 14 events by the end of the study period.

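### Logistic regression with odds ratios is prescribed for tissue-marker changes, although the stated objective is to correlate them with MRI changes; on a graded marker scale this costs information

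*Protocol article*

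**What the plan says.** The Statistical analysis section opens by naming two model families, logistic and Cox. Five questions follow. The fifth asks whether thresholds and temporal changes of the fMRI parameters "can predict changes in immunohistochemical markers of hypoxia and epithelial mesenchymal transition". The next paragraph covers the whole list: "For each of the above regression analyses, a univariate logistic regression reporting the OR with 95% CI and p value from the likelihood ratio test". Covariates that pass a univariate screen at p<0.1 then enter a forward conditional logistic model, with significance judged at p<0.05. The final prognostic model is assessed by sensitivity, specificity and area under the ROC curve.

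Two other places describe the same work as correlation. The Secondary outcomes include: "To correlate temporal changes in quantitative MRI parameters during CRT with molecular markers from tissue biopsies and CTCs isolated from peripheral blood samples". The Translational biological assessment section, after listing the stains (CA IX, GLUT-1, VEGF, CD44, SOX-2), says: "These molecular markers at various time points will be correlated with imaging parameters and evaluated independently and in combination with respect to prognostic impact". Tissue comes from the diagnostic biopsy and from one taken at brachytherapy, so a marker change needs both. The article does not give the scoring scale of the stains.

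On size, the Sample size and power section says "The proposed sample size of 40 patients is a convenience-based sampling" and that "formal statistical power calculations have not been performed".

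**The concern.** The objective asks how strongly imaging change and marker change move together. The prescribed method gives the odds of falling on one side of a split in marker change. Cox regression is no alternative here, because the difference between two biopsy scores is not a time to an event. Logistic regression is therefore the only model that the section provides for this item.

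Two things are at stake. First, if the stains are scored on more than two levels, splitting the change discards grading from at most 40 biopsy pairs. Second, the odds ratio changes with the place of the split. The sample size section says that exploratory studies help to size later ones. A cut-dependent odds ratio can size a later study that uses the same cut, but it is less portable than a correlation or slope with its confidence interval.

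**Working it through.** **The plan's own figures.** Accrual: 30 patients a year × (1 − 0.30) = 21, and 21 × 2 years = 42, against the planned 40. Events: 40 × 0.35 = 14. Both reproduce. The 14 events do not bear on the marker analysis, and no power or effect size is given for it.

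**Does the text lead to a cut?**
1. The outcome of item five is a change in marker staining.
2. Of the two model families named, Cox cannot apply.
3. The rule for all items is logistic regression with an odds ratio, then a forward conditional logistic model. That procedure points to a binary outcome.
4. A binary outcome made from a graded change needs a split.

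The thresholds named in item five belong to the fMRI predictors, so they do not explain a split of the outcome.

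**What a split would cost: inputs**
- From the article: n = 40.
- Assumed: 40 complete biopsy pairs; bivariate normal imaging and marker changes; true correlation r of 0.3, 0.4 or 0.5; a univariate test at two-sided 0.05; the imaging variable kept continuous.

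**Hand check for Pearson.** Power ≈ Φ(atanh(r)·√(n−3) − 1.96). For r = 0.4: 0.4236 × 6.083 − 1.96 = 0.617, so power is 73%. The same formula gives 47% at r = 0.3 and 92% at r = 0.5.

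**Simulation.** Power in per cent, from two independent simulations; the first used 20,000 runs per cell:

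| Method | r = 0.3 | r = 0.4 | r = 0.5 |
|---|---|---|---|
| Pearson | 47; 48 | 74; 76 | 92; 92 |
| Spearman, continuous score | 43; 43 | 68; 70 | 88; 89 |
| Spearman, five levels | 41; 42 | 67; 67 | 87; 87 |
| Spearman, three levels (second simulation only) | 38 | 62 | 83 |
| Logistic likelihood ratio test, median cut | 34; 33 | 55; 56 | 77; 77 |
| Logistic, cut at 75th percentile (first simulation only) | 29 | 48 | 69 |

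**Loss from the median cut, in points at r = 0.3 / 0.4 / 0.5** (differences taken before rounding in the first simulation)
- Against Pearson: 13/19/15 and 15/20/15, so about 13–20.
- Against Spearman on a continuous score: 9/13/12 and 10/14/12, so about 9–14.
- Against Spearman on five levels: 7/11/10 and 9/11/10, so about 7–11.
- Against Spearman on three levels: 5/6/6, and 4/6/5 in a further set of 4,000 runs, so about 4–7 once rounding and simulation error are allowed for.

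The median cut is made on the underlying continuous change in every row. A coarse score could rarely be split exactly at its median.

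**Sensitivity.** A cut at the 75th percentile costs 18/26/24 points against Pearson. Over r = 0.2 to 0.6 and cuts from the 50th to the 75th percentile, the loss against Pearson or Spearman runs from about 3 to 26 points. If only 28 pairs were complete (40 × 0.70, an illustration) and r = 0.4, power is 57% for Pearson, 52% for Spearman and 42% after a median cut.

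**Type I error.** At r = 0 and n = 40 the correlation tests reject 5.0% of the time and the median-cut logistic test 5.8%. The advantage of the uncut analysis is therefore not bought with false positives.

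**The case against.** The strongest reply is that the text is less rigid than it looks. Four parts of it stand.

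- **Scale.** The article lists stains without a scoring scale. A marker whose outcome is truly positive or negative suits logistic regression, and the loss disappears. A reader might infer that graded changes are certainly being cut; the document does not establish this.
- **Form of the model.** The article never says binary. A proportional-odds model is also logistic, reports an odds ratio and needs no single cut. A reader might infer that a cut is unavoidable. It is only the more natural reading, supported by the forward conditional step. The sensitivity and specificity sentence concerns the final prognostic model and does not settle the matter.
- **Silence.** A scale or cut may sit in a full protocol or SAP not shown, so the absence of a named cut is no finding. Nor does the statistical section say that the correlation is abandoned. It may be intended alongside the regression. For the same reason, the absence of VEGF and circulating tumour cells from the fifth analysis is not raised as an error.
- **Power.** A reader might want one figure for the loss. The article supports none: it gives no marker effect size and disclaims power calculations. The comparisons above are also univariate at 0.05. They do not reproduce the planned p<0.1 screen and forward selection, or the thresholding of fMRI parameters.

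What the reply does not remove is the mismatch. The article makes a positive choice of model for every listed analysis, and that model does not estimate the quantity named in its own objective. An SAP that followed the rule would inherit the problem; one that used correlation for this item would depart from the rule.

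**Conclusion.** The point holds as a mismatch between a stated method and a stated objective. The blanket logistic rule covers prediction of marker change, no correlation, rank or linear method is named, and the objective is correlation. That conclusion rests on the text alone.

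The size of the loss is conditional on a graded scale, the binary reading, 40 complete pairs and true correlations of 0.3 to 0.5. On those terms a median cut costs from about 4 points of power (against Spearman on a three-level score) to about 20 (against Pearson on a continuous score), and less favourable cuts cost more. Severity is minor: this is a secondary, exploratory analysis in a convenience sample, and the primary outcome is untouched.

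**What to change.** In the Statistical analysis section, exempt the fifth analysis from the rule that applies logistic regression to every item, and analyse each marker on the scale on which it is scored:

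- Report a Spearman correlation with 95% CI between MRI change and marker change.
- Support it with a regression of the brachytherapy-biopsy score on MRI change, adjusted for the diagnostic-biopsy score: linear for a continuous score, proportional-odds for an ordinal one.
- Keep binary logistic regression only for markers truly scored positive or negative.

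This brings the section into line with the translational section and the secondary outcomes. It needs a wording change and standard analyses of data already being collected, with no extra patients, samples or scans. The downside is that these results would be reported mainly as correlations or slopes, not in the odds-ratio format of the other analyses.
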